### Data monitoring

This is the first clinical trial to evaluate the topical application of *T. fagifolia* Mart. extract in ulcers, providing initial data on its safety in humans. All procedures related to ulcer assessment, extract application, and adverse event reporting will be prospectively recorded using standardized forms. Safety monitoring will include active and systematic surveillance of local reactions at the lesion site (erythema, pain, pruritus, increased exudate, and signs of infection), as well as systemic adverse events potentially associated with the intervention. All events will be documented, classified according to severity and causality, and managed in accordance with predefined clinical protocols. Serious or unexpected adverse events will be promptly reported to the Research Ethics Committee, in compliance with current national regulations.

Participants will be monitored at each treatment session for signs of secondary infection throughout the study. At each session, lesions will be systematically assessed by a trained evaluator for clinical indicators of infection, including purulent exudate, malodor, dark discoloration, tissue necrosis, perilesional cellulitis, and systemic signs such as fever. The diagnosis of infection will follow the criteria established by the Infectious Diseases Society of America (IDSA) [33], requiring the presence of at least two local signs of inflammation or infection. In cases where infection is suspected or confirmed, the participant will be promptly referred to an independent physician, not involved in the intervention, for appropriate clinical management. The intervention protocol may be adjusted or discontinued if clinically indicated to ensure patient safety (Table 3).

**Table 3 Tab3:** Recruitment, interventions, and assessment schedule according to the recommendations for interventional trials (SPIRIT)

STUDY PERIOD							
	Enrollment		Post-allocation (weeks)				Post-intervention
TIMEPOINT	Recruitment	Allocation	Basiline	5 W	10 W	Once a week	t_x_
ENROLLMENT:							
* Recruitment*	X						
* Selection Criteria*	X						
* Allocation*		X					
INTERVENTIONS							
* CG*			X	X	X		
* G1*			X	X	X		
* G2*			X	X	X		
ASSESSMENTS:							
* Evaluation form*			X				
* Ulcer reduction rate*			X	X	X		
* Clinical Response Analysis*			X	X	X		
* Glycemic level assessment*			X			X	
* University of Texas Rankings*			X	X	X		

### Statistical analysis

All statistical analyses will be conducted according to the intention-to-treat principle. Data will be tabulated in spreadsheets (Excel package) and analyzed using SPSS version 29 (Statistical Package for the Social Sciences). Sociodemographic data will be presented as descriptive statistics, absolute values and percentages, or mean and standard deviation (median and interquartile range). Normality will be assessed using the Kolmogorov–Smirnov test. The chi-square test will be applied for categorical data. To analyze differences between groups, a one-way ANOVA or the Kruskal–Wallis test will be performed. Intragroup analysis will be conducted using one-way repeated-measures ANOVA or the Friedman test. Statistical significance will be set at *p* < 0.05, and results will be presented in tables. The cumulative proportion of responders will be calculated considering a 50% healing rate, based on the article previously published by the group, and analyzed as described by Farrar et al. [22, 31]. In studies with graded outcomes, the mean difference between the curves of two groups represents the absolute risk reduction (ARR), from which the number needed to treat (NNT = 1/ARR) can be derived.

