## Methods

### Study design and recruitment

This is a randomized, single-blind experimental study with blinding applied to the evaluator. In this study, we propose a comparison between a new dressing and PBM in non-infected diabetic ulcers over a period of 10 weeks (20 interventions). *Terminalia fagifolia* Mart. sample was collected in Timon City, Maranhão State of Brazil, during a rainy summer to obtain the plant extract, that will be used at a concentration of 1 mg/mL, defined based on prior experimental optimization conducted by the research group, considering physicochemical stability and preliminary biological activity. The species was identified and the voucher deposited in the Delta do Parnaíba Herbarium (HDelta), at the Parnaíba Delta Federal University (n° 6979). Furthermore, the study was registered in the National System for the Management of Genetic Heritage and Associated Traditional Knowledge (SisGen) under number A7851F5. Detailed formulation parameters are currently under patent protection, and a comprehensive description of the standardization process will be reported in a separate study under peer review. Detailed formulation parameters are currently under patent protection, and a comprehensive description of the standardization process will be reported in a separate study under peer review. In the control group, GaAs 904 nm, 70 mW, and an energy density of 10 J/cm² (ENDOPHOTON KLD) will be used in pulsed mode, as described in a previous study [22]. This study was approved by the local Research Ethics Committee (Protocol 6.499.992) and the Brazilian Registry of Clinical Trials (ReBEC) (RBR-25ng5pt) and will be conducted in accordance with the Declaration of Helsinki and the SPIRIT [23] (Standard Protocol Items: Recommendations for Interventional Trials) and CONSORT [24] (Consolidated Standards of Reporting Trials) guidelines.

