### Sample size

The sample size was calculated using G*Power 3.1.9.4 software, based on the primary outcome of wound area reduction [25]. A repeated-measures ANOVA (F-test) was used to account for the interaction between within-subject factors (three time points: baseline, 5 weeks, and 10 weeks) and between-subject factors (three groups: CG, G1, and G2). The analysis considered a statistical power of 0.90, an alpha level of 0.05, and an effect size of 0.31. Based on these parameters, a total sample size of 93 participants was estimated. Assuming a 10% loss to follow-up, 102 volunteers will be recruited (34 volunteers per group).

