### Primary outcome

#### Ulcer reduction rate

The primary variable will be the rate of ulcer size reduction over 10 weeks. After the initial assessment, the DFUs will be identified, and the area will be photographed alongside a paper ruler, which will serve as a calibrator for the ImageJ software (Fig. 2) [28, 29]. DFUs will be assessed at three time points: pre-intervention (baseline), after 5 weeks (10 sessions), and after 10 weeks (20 sessions). The calculation of the reduction rate will follow the same parameters used by Ahmed and Irfan [30], represented by the formula: $$\:\frac{Af-Ai}{Ai}\:x\:100$$. Here, Ai and Af denote the initial and final ulcer areas, respectively. Ulcer area measurements will be performed by a blinded independent evaluator, who will be unaware of group allocation. The primary outcome will be compared between groups and across time points using repeated-measures analysis.

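### The between-group test is left as ANOVA or Kruskal–Wallis with only a normality test to choose between them, and neither is the repeated-measures comparison promised for the primary outcome

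*Protocol article*

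**What the plan says.** All references are to the protocol article.

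- **Statistical analysis**, normality: "Normality will be assessed using the Kolmogorov–Smirnov test". No level, unit (arm, pooled data, residuals, visit) or decision rule is given.
- **Statistical analysis**, between groups: "To analyze differences between groups, a one-way ANOVA or the Kruskal–Wallis test will be performed".
- **Statistical analysis**, within groups: "Intragroup analysis will be conducted using one-way repeated-measures ANOVA or the Friedman test".
- **Ulcer reduction rate** (primary outcome): "The primary outcome will be compared between groups and across time points using repeated-measures analysis". The outcome is the percentage change (Af − Ai)/Ai × 100, assessed at baseline, 5 weeks and 10 weeks.
- **Sample size**: "A repeated-measures ANOVA (F-test) was used to account for the interaction between within-subject factors" (three time points) and between-subject factors (three groups), with "a statistical power of 0.90, an alpha level of 0.05, and an effect size of 0.31". From this, "a total sample size of 93 participants was estimated", raised to 102, or 34 per group.

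**The concern.** Two things are left open. First, the analysis section lists pairs of alternative tests, and a normality test on the trial's own data is the only selector in sight. ANOVA compares means and Kruskal–Wallis compares rank distributions, so the data would settle which question is answered. Second, two other sections describe a group-and-time repeated-measures comparison that the analysis section does not list.

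The shape of the outcome can be foreseen from its formula. The value stops at −100% when an ulcer closes and has no upper limit when an ulcer grows. A suitable analysis can therefore be named now, without a look at the data. Until it is, a significant or a null primary result could depend on which branch was taken, and a reader could not tell which test had been intended.

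**Working it through.** **1. The three sections side by side**

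| Section | Test for the between-group comparison | Time |
|---|---|---|
| Sample size | Repeated-measures ANOVA F-test, described with the group-by-time interaction | Three visits |
| Ulcer reduction rate | Repeated-measures analysis, between groups and across time | Three visits |
| Statistical analysis | One-way ANOVA or Kruskal–Wallis | Visit not stated |

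The only repeated-measures ANOVA in the third section works within one group at a time, so it cannot compare groups.

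**2. The plan's own figure**

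Inputs from Sample size: f = 0.31 (taken as Cohen's f, f² = 0.0961), α = 0.05, power 0.90, 3 groups, m = 3 visits. The correlation ρ and sphericity factor ε are not stated and are assumed here.

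- Between-groups effect averaged over visits: λ = f²·N·m/(1 + (m − 1)ρ). With N = 93 and ρ = 0.5, λ = 0.0961 × 93 × 3/2 = 13.41 on 2 and 90 df, and power is 0.907. This reproduces 93.
- Group-by-time interaction: λ = f²·N·m·ε/(1 − ρ). With ρ = 0.5 and ε = 1, N = 30 is enough (λ = 0.0961 × 30 × 3/0.5 = 17.30). Among the values tried (ρ from 0 to 0.7, ε of 1 or 0.5), 93 comes out only at ρ = 0 and ε = 0.5.
- One-way ANOVA at a single visit, same f: λ = f²·N. At N = 93, λ = 8.94 and power is 0.75. At N = 102, λ = 9.80 and power is 0.79. Power of 0.90 needs N = 135.

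So 93 can be reproduced from a repeated-measures test. The single-visit test named in the analysis section would have clearly less than the stated power at the same f.

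**3. How often the choice between the two tests matters**

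Assumptions, none of them from the article: 34 per arm; log area ratio normal with SD 0.6, 0.8 or 1.0; median ratio 0.5; ratio below 0.1 counted as closed; under the alternative, one arm better by 0.5 on the log scale.

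- ANOVA and Kruskal–Wallis fall on opposite sides of p = 0.05 in about 7%, 21% and 25% of trials at the three SDs. Over repeated runs the range was 7–26%.
- With no true effect, reporting whichever test is significant rejects in about 6–7.5% of trials. Six other assumed shapes (normal, t with 5 df, two lognormals, beta, percentage reduction capped at 100) gave 5.9–7.1%.

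**4. How the gated rule behaves when it is followed**

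Assumed rule: Kolmogorov–Smirnov per arm at 5%, Kruskal–Wallis if any arm rejects, otherwise ANOVA. "Uncorrected" and "Lilliefors" refer to the critical value used.

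- Type I error: 4.6–5.8% in the area-ratio model; 4.9–5.4% over the six other shapes with Lilliefors critical values.
- Power in the area-ratio model:

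| SD | Always Kruskal–Wallis | Gate, uncorrected | Gate, Lilliefors |
|---|---|---|---|
| 0.6 | 0.94 | 0.92 | 0.94 |
| 0.8 | 0.73 | 0.71 | 0.73 |
| 1.0 | 0.53 | 0.52 | 0.53 |

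The largest loss is about 2 points. Over the other six shapes the Lilliefors gate also stayed within about 2 points of the better fixed test. The uncorrected gate did worse in two uncapped shapes under a plain location shift: t with 5 df (0.81 against 0.87) and lognormal with σ = 0.5 (0.83 against 0.93).

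**The case against.** The strongest reply is that the primary outcome already has its method. The Ulcer reduction rate section assigns it a repeated-measures analysis, and the analysis section never ties ANOVA or Kruskal–Wallis to it. Nor does that section say that the Kolmogorov–Smirnov result makes the choice. Both points are correct. A reader might infer that a normality test picks the primary test; that is the natural reading, but it is an inference. What stands is that the section meant to specify the analysis has no model that delivers the promised comparison, and its only between-group tests for continuous data are the open pair.

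Three stronger readings are not supported:

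- **That the rule performs badly at 34 per arm.** Followed faithfully, it keeps type I error near 5% and, under the area-ratio model, nearly all the power. The power gap between always using ANOVA and always using Kruskal–Wallis does not describe a rule that switches between them.
- **That an uncorrected Kolmogorov–Smirnov test will be used.** The article does not say so. Version, level and unit are details that an article may leave to the full plan.
- **That an unblinded analyst makes the choice.** The article says "This is a randomized, single-blind experimental study with blinding applied to the evaluator" and is silent on the analyst. Silence in a condensed article is not evidence that the analyst knows the arms.

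It may also be said that any choice of test can wait for the statistical analysis plan. That would hold if the article were silent. It is not: it states a pair of tests in one section and a different analysis in two others.

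**Conclusion.** The point holds in limited form. The article does not fix whether the primary comparison concerns means or ranks, or a single visit or repeated measures, and its sections disagree on the second question. Under the assumed skewed shapes with closure, the two permitted tests give different verdicts in about 7–26% of trials with a true effect, and unrestricted choice between them raises type I error to about 6–7.5%. Those sizes rest on the assumed distribution and treatment effect. The mismatch between sections rests on the text alone.

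This is a lack of pre-specification, not a large distortion of error rates. It should be corrected because the correction is cheap and the outcome's shape is known in advance.

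**What to change.** 1. Remove the normality test as a rule for choosing between tests. Diagnostics may still be reported.
2. Name one primary between-group analysis of ulcer area reduction that agrees with the Sample size and Ulcer reduction rate sections. One example is a group-by-time repeated-measures or mixed model with a stated week-10 contrast. Use a scale, or a robust method, suited to an outcome bounded at complete closure. Percentage change is zero for everyone at baseline, so say whether the model uses area at three visits or percentage change at two.
3. Pre-specify a rank-based test, such as Kruskal–Wallis at week 10, as a sensitivity analysis. Making it the primary analysis would conflict with the repeated-measures comparison on which the trial was sized.
4. Name one test for glucose.

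The cost is a few sentences and no new data. The one downside is that the primary and sensitivity p-values may occasionally differ; with their roles fixed beforehand, the primary one decides.

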### University of Texas rankings

To identify changes in ulcer depth, ulcer images will be obtained before the intervention (baseline), after 5 weeks (10 sessions), and after 10 weeks (20 sessions), and classified using the University of Texas Wound Classification System [32]. Volunteers will be grouped into A1 and C1 (superficial ulcers), A2 and C2 (ulcers involving the tendon or joint capsule), and A3 (ulcers involving the bone). This classification will be used for longitudinal assessment of ulcer depth and compared between groups over time.

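### Ulcer depth is to be compared between groups over time, but no test is assigned to it and no listed between-group test uses the baseline grade

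*Protocol article*

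**What the plan says.** The University of Texas rankings section makes ulcer depth a secondary outcome. On timing: "ulcer images will be obtained before the intervention (baseline), after 5 weeks (10 sessions), and after 10 weeks (20 sessions". On the scale: "Volunteers will be grouped into A1 and C1 (superficial ulcers), A2 and C2 (ulcers involving the tendon or joint capsule", with A3 (bone) as the third and deepest group. On use: "This classification will be used for longitudinal assessment of ulcer depth and compared between groups over time".

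The Statistical analysis section names tests by type of data or contrast, and not by outcome:

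- On data type, it states: "The chi-square test will be applied for categorical data".
- For contrasts between the arms, it offers a choice of one-way ANOVA and Kruskal-Wallis.
- For change inside each arm, it states: "Intragroup analysis will be conducted using one-way repeated-measures ANOVA or the Friedman test".

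Depth is not mentioned there. The repeated-measures comparison across groups and time points in the Primary outcome section is stated for ulcer area only.

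**The concern.** The stated question is whether depth changes differently between the arms. That needs a between-group analysis that uses where each ulcer started. The listed methods either compare groups without reference to baseline, or look at change inside one group at a time.

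Three things are at stake. A depth effect may be missed although the baseline grade that would help to show it is already scheduled. If chi-square is applied to the week-10 grade, the ordering of the grades is discarded as well. And because no test is assigned, the choice between chi-square and Kruskal-Wallis for depth stays open until the data are seen.

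**Working it through.** **1. Question against listed tests**

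| Listed method | Compares groups | Respects grade order | Uses baseline grade, as listed |
|---|---|---|---|
| Chi-square | yes | no | no |
| One-way ANOVA | yes | only through numeric scores | no |
| Kruskal-Wallis | yes | yes | no |
| Repeated-measures ANOVA or Friedman | no (intragroup) | Friedman yes | only within one group |

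No row compares change between groups. Stacking the three visits in one chi-square table would count each participant three times and break independence.

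**2. Arm size**

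The protocol gives no power figure or grade distribution for depth, so there is no depth figure to reproduce. The Sample size section concerns wound area: "a statistical power of 0.90, an alpha level of 0.05, and an effect size of 0.31", from which "a total sample size of 93 participants was estimated". The 93 reproduces as a between-groups test with three measurements and an assumed correlation of 0.5:

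λ = f²·N·m / (1 + (m − 1)ρ) = 0.31² × 93 × 3 / (1 + 2 × 0.5) = 13.4, on 2 and 90 degrees of freedom, power 0.907.

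It is used here only for arm sizes: 93/3 = 31 after losses and 102/3 = 34 recruited.

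**3. Simulation with one-level shifts (inputs assumed)**

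The set-up is 31 per arm with the three documented levels. An ulcer improves by at most one level, and a superficial ulcer cannot move lower. Rank ANCOVA means ranks of the week-10 grade regressed on group and baseline rank.

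With baseline depth 50/35/15% and improvement probabilities by arm of (0.3, 0.3, 0.6), (0.3, 0.45, 0.6) and (0.2, 0.3, 0.5), rank ANCOVA has power 0.35, 0.26 and 0.30. Week-10 chi-square has 0.08 to 0.10.

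| Set of assumed inputs | Chi-square, week 10 | Kruskal-Wallis, week 10 | Rank ANCOVA |
|---|---|---|---|
| Main set | 0.08–0.17 | 0.11–0.21 | 0.27–0.46 |
| Baseline mixes 50/35/15, 70/20/10 and 34/33/33 | 0.05–0.13 | 0.07–0.15 | 0.12–0.47 |

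Type I error is about 5% for all three methods.

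**4. Simulation with a proportional-odds model (inputs assumed)**

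The set-up is 34 per arm, three levels, latent correlation between baseline and week 10 of 0.5 or 0.8, three grade mixes, odds ratios by arm of (1, 1, 3), (1, 1, 4) and (1, 2, 4), and 800 runs per scenario. Selected results:

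| Control grades at week 10 | Odds ratios | Correlation | Chi-square | Kruskal-Wallis | Baseline-stratified rank test | Chi-square / stratified |
|---|---|---|---|---|---|---|
| 60/28/12% | 1, 1, 3 | 0.5 | 0.384 | 0.505 | 0.551 | 0.70 |
| 60/28/12% | 1, 1, 3 | 0.8 | 0.405 | 0.545 | 0.768 | 0.53 |
| 40/35/25% | 1, 1, 4 | 0.5 | 0.731 | 0.810 | 0.868 | 0.84 |
| 75/20/5% | 1, 1, 3 | 0.8 | 0.230 | 0.320 | 0.446 | 0.52 |

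Over all scenarios with an effect, chi-square keeps 65–91% of the Kruskal-Wallis power and 52–84% of the baseline-stratified power. The stratified ratio is 0.62–0.84 at correlation 0.5 and 0.52–0.78 at 0.8. With 31 per arm, correlation 0.8 and a baseline-adjusted proportional-odds model, one scenario gives 0.35 against 0.76, a loss of 1 − 0.35/0.76 = 54%.

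**The case against.** **Chi-square is never assigned to depth.** It follows the sentences on sociodemographic data and normality, and Kruskal-Wallis, which respects order, is listed for differences between groups. This stands. A reader might infer that chi-square is the planned test for depth, but the text does not say so. The fault is that nothing is assigned and that neither candidate, as listed, uses the baseline grade.

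**Chi-square could be run on change.** A table of improved yes/no against baseline would compare change. In the one-level model with a fourth, lower level added, it has power 0.70, 0.55 and 0.62 in the three scenarios, against 0.68, 0.54 and 0.60 for rank ANCOVA. This also stands: the loss comes from analysing the week-10 grade alone. But the plan defines no such table.

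**The loss is not always large.** A reader might infer that most of the power is lost. That happens under one-level shifts, where the week-10 grade tracks baseline closely, but under proportional odds the loss is usually below half. Powers of 0.54–0.69 for rank ANCOVA arise only with the fourth level, which the protocol's three depth groups do not include. With three levels, the better analysis would also often miss the effect.

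**Small expected counts.** With few deep ulcers, most tables have an expected count below 5. Even so, simulated type I error stayed near 5%, so this does not make chi-square invalid here.

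**A condensed article leaves detail to the analysis plan.** This is fair for the choice of model and the handling of sparse cells. But the article does set out a list of tests, and that list does not match a comparison that the article itself states.

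**Conclusion.** The point holds as a mismatch between a stated comparison and the listed tests, for a secondary outcome. Depth over time between groups has no assigned analysis, and no listed between-group test, as described, takes the baseline grade into account. With randomised groups the consequence is lost precision, not bias.

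The size cannot be fixed from the document. Under one-level shifts, baseline adjustment raises power from roughly 0.1–0.2 to roughly 0.3–0.5, and by less when most ulcers start superficial. Under proportional odds with latent correlation 0.5 to 0.8, week-10 chi-square gives up about 16–48% of the baseline-stratified power. The direction was the same in every scenario with an effect, and the gain grows with the correlation between baseline and week-10 grade. This is an improvement worth making, and it does not threaten the trial's main conclusion.

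**What to change.** Add one sentence on depth to the Statistical analysis section. For example: ulcer depth (three ordered groups) at week 10 will be compared between groups with a proportional-odds model, or ANCOVA on ranks, with group and baseline depth as terms; week 5 will be analysed in the same way as supportive. Keep chi-square for unordered categorical data such as baseline characteristics.

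The cost is wording only. The baseline, week-5 and week-10 grades are already in the assessment schedule (Table 3), and the analysis can be run in SPSS, which the protocol names. The small downside is the proportional-odds assumption, which the rank version avoids. Making the choice before the data are seen also closes the open choice between chi-square and Kruskal-Wallis.

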### Initial assessment

After meeting the eligibility criteria and signing the informed consent form, participants will have their lower limbs assessed by an external evaluator. A form developed by the researcher will be used to collect data such as personal information, clinical history, capillary blood glucose, body mass index (BMI), time since DM diagnosis, and ulcer duration. In addition, the exact affected area will be identified and recorded during the assessment.

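### The Sample size, Primary outcome and Statistical analysis sections do not name the same primary test, and the tests finally listed contain no group-by-time term

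*Protocol article*

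**What the plan says.** Three places in the protocol article bear on the primary test.

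- **Sample size:** "A repeated-measures ANOVA (F-test) was used to account for the interaction between within-subject factors" (three visits) and the three arms. Power is 0.90, alpha 0.05 and effect size 0.31, giving 93 participants, raised to 102 for 10% loss.
- **Ulcer reduction rate (primary outcome):** "The primary variable will be the rate of ulcer size reduction over 10 weeks". It is the percentage change in area relative to baseline area. On the analysis: "The primary outcome will be compared between groups and across time points using repeated-measures analysis".
- **Statistical analysis:** one-way ANOVA or Kruskal–Wallis for differences between arms. Then: "Intragroup analysis will be conducted using one-way repeated-measures ANOVA or the Friedman test". The section also states "All statistical analyses will be conducted according to the intention-to-treat principle" and "Normality will be assessed using the Kolmogorov–Smirnov test". It names no two-way or mixed repeated-measures model and no group-by-time term. It does not say which listed test is primary.

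The Initial assessment section records the affected area and "time since DM diagnosis, and ulcer duration". No covariate adjustment is mentioned.

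**The concern.** The trial's hypothesis is comparative: the combination should heal ulcers faster than either treatment alone. Two sections point to an analysis that compares arms across visits. The section that lists the tests uses repeated measures only inside each arm and compares arms only one-way.

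Three things are at stake.

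- **The primary test is open.** A week-10 ANOVA, a week-5 Kruskal–Wallis test and a group-by-time interaction can each be defended from the text. The choice between mean-based and rank-based versions also appears to wait on a normality test of the trial data.
- **The stated power may not belong to the test that is run.** The 93 comes from a repeated-measures calculation, and a one-way test at one visit uses less information.
- **The listed tests have limits.** Within-arm p-values do not compare arms. Classical repeated-measures ANOVA and Friedman, as normally run, need all three visits from each participant.

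**Working it through.** **Inputs.** From Sample size: 3 arms, 3 visits, f = 0.31 (read as Cohen's f), alpha 0.05, power 0.90, N = 93, 10% loss, 102 recruited. Assumed because not stated: correlation between visits rho = 0.5, and sphericity. All power figures below use the noncentral F distribution and refer to the overall test of three arms.

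**1. Reproducing the 93.** For the between-groups test in a repeated-measures ANOVA, lambda = f² × N × m / (1 + (m − 1) × rho).

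- At N = 93: 0.0961 × 93 × 3 / 2 = 13.41, with 2 and 90 df. Power is 0.907.
- The smallest N reaching 0.90 is 91, or 93 with equal arms. The stated figure is reproduced.

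For the interaction, which the text describes, lambda = f² × N × m / (1 − rho).

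- At N = 30: 0.0961 × 30 × 3 / 0.5 = 17.30, with 4 and 54 df. Power is 0.909, so 30 would suffice. At N = 93 the power exceeds 0.999.
- The required N is 57 at rho = 0 and 15 at rho = 0.8. Versions whose effect size is not scaled by rho need 84 to 87.

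So 93 matches the between-groups test at rho = 0.5 rather than the interaction that the sentence describes. The interaction formula gives 93 only with rho = 0 and the strongest departure from sphericity (epsilon 0.5).

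**2. Power of the listed between-group test.** For one-way ANOVA at one visit, lambda = f² × N with 2 and N − 3 df, carrying f = 0.31 over unchanged.

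| N | lambda | power |
|---|---|---|
| 93 | 8.94 | 0.753 |
| 102 | 9.80 | 0.794 |
| 135 | 12.97 | 0.901 |

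With equal arms, about 135 evaluable participants are needed for 0.90. The gap from step 1 is a factor of 1.5 in lambda (13.41 / 8.94).

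**3. What separate within-arm tests can show.** Suppose three arms heal identically and each within-arm test has 80% power (an assumption). The chance that the arms disagree on significance is 1 − 0.8³ − 0.2³ = 1 − 0.512 − 0.008 = 0.48. A simulation with 31 per arm and rho = 0.5 (4,000 runs) gives:

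| Assumed fall in every arm (SD) | Chance of disagreement |
|---|---|
| 0 | 14% |
| 0.3 | 61% |
| 0.5 | 65% |
| 0.6 | 42% |
| 0.8 | 6% |

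The figure depends strongly on the assumed effect. It shows only that differing within-arm verdicts are no evidence of a difference between arms.

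**4. Incomplete follow-up.** Ten percent of 102 is about 10 participants. A test that needs all three visits would also set aside the week-5 area of anyone who misses only week 10.

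**5. What baseline adjustment could return.** Adjusting for a covariate with correlation r to the outcome divides lambda by 1 − r². At N = 93, with assumed r:

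| r | lambda | power |
|---|---|---|
| 0.3 | 8.94 / 0.91 = 9.82 | 0.794 |
| 0.5 | 8.94 / 0.75 = 11.92 | 0.869 |
| 0.6 | 8.94 / 0.64 = 13.96 | 0.919 |

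**The case against.** The strongest reply is that nothing has been abandoned. The Primary outcome section still promises the repeated-measures comparison, and the Statistical analysis section does not withdraw it. That is right: this is an inconsistency, not a replacement. It still has to be resolved, because the section that lists the tests is specific and does not list that one.

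A reader might go further and infer four things that the document does not support.

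- **That the plan gives no unbiased answer.** The primary variable is percentage change, and a one-way test of it at week 10 is a valid randomised comparison.
- **That the plan is not intention-to-treat.** The section states "All statistical analyses will be conducted according to the intention-to-treat principle" and nowhere says that incomplete cases are dropped. Handling of missing areas may sit in an analysis plan that is not shown. Listwise deletion is the usual behaviour of the named tests, not a stated rule. Nor does Data monitoring say that area measurement ends when infection changes or stops treatment.
- **That baseline area is ignored.** It is the denominator of the outcome: "Here, Ai and Af denote the initial and final ulcer areas, respectively". Only covariate adjustment is absent, and its absence costs precision without biasing a randomised comparison.
- **That within-arm p-values will be read as treatment differences.** The protocol does not say so, and it lists a separate between-arm test.

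It is also fair to say that choosing a test after a normality check is common practice. That makes it a lesser weakness, though it leaves the primary test to be picked from the data.

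**Conclusion.** The point holds as an internal contradiction: three sections do not agree on one primary test, and the listed tests include no joint group-by-time analysis. Comparing the texts is enough to establish this, with no numerical assumption.

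The cost in power is conditional. If f = 0.31 applies unchanged at a single visit, the listed one-way test has power of about 0.75 at 93 and 0.79 at 102, against the stated 0.90. Matching the 93 to the between-groups test rests on rho = 0.5, which the protocol does not give.

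Two further points stand in modest form. The within-arm tests cannot show a difference between arms. The named repeated-measures tests, as normally run, fit poorly with the stated intention-to-treat principle and the expected 10% loss.

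**What to change.** In Statistical analysis, name one primary analysis and make the other two sections refer to it.

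- **Primary:** a linear mixed model (SPSS MIXED) of percentage area change at weeks 5 and 10. Baseline change is zero by definition, so it is not an outcome row. Fixed effects are group, visit, group-by-visit and log baseline area, with ulcer duration optional. Include every randomised participant with any post-baseline area, in the assigned arm. The week-10 group contrasts are primary.
- **Sensitivity:** a rank-based analysis, specified in advance, instead of choosing the test from the Kolmogorov–Smirnov result.
- **Within arms:** describe changes with confidence intervals and no tests.
- **Sample size:** say which test the 93 refers to, and restate the power for the week-10 contrasts with the assumed correlations. The model does not restore 0.90 by itself. Under the assumptions above, the overall week-10 comparison reaches it at N = 93 only if the baseline covariates correlate with the outcome somewhere between 0.5 and 0.6 or more.

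The cost is rewording and slightly more analysis work. The software is already named, baseline area and ulcer duration are already collected, and no visit is added.
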